### Outcome measurements

2.8.

Patients must have an indication for the surgery. The primary outcome variable is the JOA score. The secondary outcome variables include the VAS score, physical examination findings, length of hospital stay, expenses, and complications. Outcomes will be measured on the first postoperative day, and thereafter at the 1st week, and at 1, 3, 6, 12, and 24 months after surgical treatment. A physical examination will be conducted after 1 week, 1 month, and 12 months from the day of the surgery (Table 1). The non-inferiority margin for the primary outcome is five.

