### Primary outcome

2.9.

We will use the JOA score to assess the primary outcome (12, 13). It is divided into the cervical and JOA scores, including subjective symptoms, clinical signs, daily activities, and bladder function. Each item had one or more problems. The total score of the JOA was 29, and the total JOA score of the cervical spine was 17. The lower the score, the more obvious the dysfunction. The outcome parameters will be assessed using validated questionnaires and physical examination. Data from the questionnaires will be collected at 1 week and at 1, 3, 6, 12, and 24 months after the surgery by the research nurse.

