### Secondary outcome

2.10.

Secondary outcomes include the gross tumor resection(GTR) rate, tumor recurrence rate, VAS, assessment of back and leg pain at rest, physical examination, length of hospital stay, expenses, and complications. One of the secondary outcomes was the VAS of pain. Perceived pain intensity was measured using the VAS score [pain scale ranging from 0 (no pain) to 100 mm (the worst pain imaginable)] (14). The pain will be assessed because most patients have pain in different regions. A physical examination will be conducted at 1, 6, and 12 months after the surgery. This will include the sphincter function test, muscle strength exercise, patellar and Achilles tendon reflex assessment, and sensory assessment of the affected spinal region. Muscle strength will be scored on a scale ranging from zero (no contraction) to five (normal muscle strength) (15).

The cost-effectiveness of the hospital stay will be evaluated by summarizing the cost of the surgical procedure and the number of days before discharge. The cost of the additional procedures in case of complications will be added to the total cost of the patient's hospital stay. The primary cost of treatment will include the cost of hospital admission, surgery, medication, rehabilitation, and other healthcare utilization. The details of these charges will be registered in a diary. Immediately after the operation, a systematic assessment of complications (including cerebrospinal fluid leakage, venous thromboembolism, wound infection, urinary tract infection, hematoma, and progressive neurological deficit) will be conducted by the surgeon and research nurse until patient discharge. Surgical data will include intraoperative spinal cord and nerve root injury, operative time, and intraoperative blood loss.

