### Sample size calculation

2.11.

The sample size for this study was calculated based on the JOA scores. Based on the preliminary data of our department, the mean difference and SD for the JOA used in the sample size calculation were as follows: mean 21.7, SD 5.8. The sample size for non-inferiority trials was calculated using the following: (1) significance level (alpha) of 0.05 and (2) power (beta) of 90%. We estimated that 112 patients would need to be included in each group. Accounting for 10% attrition and the actual situation of each participating center, 280 patients will be recruited in total. We intend to recruit patients within two years. Recruitment for the study began in October 2021.

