### Statistical analysis

2.12.

All data will be analyzed according to the intention-to-treat principle (16, 17). The baseline data will be compared and analyzed using descriptive statistics [mean (SD), proportion, or median (range)] to determine whether balanced groups were obtained after randomization. Student's *t*-test or Mann–Whitney's *U* test will be used to compare continuous variables. Categorical variables will be compared using *χ*^2^ or Fisher's exact tests. All comparative analyses will be reported with point estimates [means (SD) or odd ratios (ORs)], 95% CIs, and *p*-values. Statistical significance will be set at *p *< 0.05. Non-inferiority margins will be set as listed in Table 2. Statistical analysis will be performed using appropriate statistical software (e.g., SPSS version 22.0 or Stata).

**Table 2 T2:** Non-inferiority margins.

Outcome measurements	Expected differences	Non-inferiority margin
JOA	<5	5
VAS	<5	5
muscle strength test	<5	5
Sphincter function test	<5	5

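### The muscle strength non-inferiority margin of 5 is the full width of its 0 to 5 scale, and the same 5 is set for a sphincter test with no stated scale

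*Protocol article*

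**What the plan says.** In the protocol article, Statistical analysis (2.12): "Non-inferiority margins will be set as listed in Table 2". Table 2 then lists four instruments, each with an expected difference below 5 and a margin of 5. Two of its rows read "muscle strength test <5 5" and "Sphincter function test <5 5". The other two rows are JOA and VAS. The table gives no units and no rationale for any instrument.

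The scales are given elsewhere:

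- Secondary outcome (2.10), muscle strength: "Muscle strength will be scored on a scale ranging from zero (no contraction) to five (normal muscle strength".
- Secondary outcome (2.10), VAS: "pain scale ranging from 0 (no pain) to 100 mm (the worst pain imaginable".
- Primary outcome (2.9): "The total score of the JOA was 29, and the total JOA score of the cervical spine was 17".
- Sphincter function test: listed as part of the physical examination in 2.10, with no numeric scale anywhere in the article.

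Outcome measurements (2.8) repeats the JOA margin: "The non-inferiority margin for the primary outcome is five".

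**The concern.** A non-inferiority margin is the largest deficit that would still be accepted as no worse. It must be small against the range of the instrument, or the test cannot tell an acceptable result from an unacceptable one. One number has been applied to four instruments with very different ranges. On the muscle strength scale that number equals the distance from no contraction to normal strength. The expected difference of less than 5 is equally empty there, because it covers every result except complete separation of the arms.

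The Introduction and Discussion put forward the hypothesis that PMTT matches laminoplasty in safety and efficacy. Muscle strength and sphincter function are direct measures of neurological harm after intradural surgery. A prespecified criterion that almost any data would meet could be cited in support of that hypothesis without being evidence for it.

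**Working it through.** **Inputs.** Margin 5 (Table 2). Muscle strength range 0 to 5 (2.10). 112 per group, and 280 in total at 1:1, so 140 per group if all are evaluable (2.11, 2.4). 95% CIs (2.12). The article does not spell out the decision rule. I take it as: non-inferior if the lower 95% limit of the mean difference, PMTT minus laminoplasty, is above -5.

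**The plan's own figure.** The 112 per group was derived for the JOA score from "mean 21.7, SD 5.8", alpha 0.05 and 90% power. With margin 5, true difference 0 and one-sided 0.025, n = 2 × [5.8 × (1.960 + 1.282) / 5]² = 28.3, so 29 per group. The stated 112 is therefore not reproduced. That is a separate matter; here 112 serves only as the number of patients analysed.

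**Step 1: margin as a share of each scale.**

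- Muscle strength: 5/5 = 100%
- JOA: 5/29 = 17%
- Cervical JOA: 5/17 = 29%
- VAS: 5/100 = 5%
- Sphincter function: cannot be computed, because no scale is stated

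On a 0 to 5 scale the mean difference cannot fall below 0 - 5 = -5, so a true deficit larger than the margin is impossible.

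**Step 2: an extreme result that passes.** The largest SD of a score bounded by 0 and 5 with mean m is √[m(5 - m)]. Take laminoplasty mean 5 (SD 0) and PMTT mean 1 (SD at most √(1 × 4) = 2), with 112 per group:

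- Lower limit = -4 - 1.96 × √(2²/112) = -4 - 0.37 = -4.37.
- This is above -5, so non-inferiority is declared with a four-grade deficit.

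**Step 3: where the criterion can fail.** Let every laminoplasty patient score 5 and let the PMTT mean be x, again with the largest SD. The criterion passes if x > 1.96 × √[x(5 - x)/112]. Squaring and dividing by x gives x > 0.0343 × (5 - x), so x > 0.166, a deficit of up to 4.83. With means placed symmetrically (x and 5 - x) the limit is also 4.83. At 140 per group it is about 4.86 to 4.87. A smaller SD would let larger deficits pass.

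**Step 4: chance of declaring non-inferiority when PMTT is truly four grades worse.** P = Φ[(5 - 4) / (SD × √(2/112)) - 1.96]. The SDs are my assumptions.

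- SD 1: Φ(7.48 - 1.96) = Φ(5.52), above 0.9999
- SD 1.5: Φ(4.99 - 1.96) = Φ(3.03) = 0.999

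**The case against.** **The metric is not fixed.** Table 2 has no units, and 2.10 does not say how grades from several muscles are combined. Section 2.12 also allows categorical tests and odds ratios. The 5 might have been meant for a summed score or as a percentage. This stands to the extent that the 100% figure depends on a mean-grade analysis. It does not rescue the table: averaging over muscles leaves the range at 5, and nothing in the article describes a sum or a percentage.

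**The harm is limited.** Muscle strength is secondary. Section 2.12 promises point estimates and 95% CIs, so a large deficit would be visible beside any verdict. Neurological harm is also captured by the JOA score, the complications in 2.10 and the adverse events in 2.10.1. All of this stands, and it limits the consequence to the non-inferiority statement itself. It does not make the stated threshold usable.

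**Stronger readings that the article does not support.**

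- A reader might infer that the muscle strength criterion can never fail. It can, when the arms are almost totally separated: with an observed deficit above about 4.83 grades, the lower limit can reach or pass -5.
- A reader might infer that the VAS comparison would probably fail at 5 mm, or would tell us nothing. The article gives no VAS SD. With 126 evaluable per group (280 × 0.9 / 2), no true difference, and assumed SDs of 15, 20 and 25 mm, power is 75%, 51% and 35% at one-sided 0.025, or about 84%, 63% and 48% at one-sided 0.05. A 5 mm margin is strict. Meeting it would be informative, and missing it would be inconclusive.
- A reader might infer that the sphincter margin is too wide. Without a scale it cannot be called wide or narrow.

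**Conclusion.** The point holds for muscle strength and, in a different way, for sphincter function. Read as a mean grade difference with a 95% CI, the muscle strength margin takes in every true difference the scale permits. A statement of non-inferiority on it would carry no information. This is a threshold the article fixes and that misleads if followed, so it is not a detail left for an analysis plan. The sphincter margin is undefined as written.

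The conclusion rests on the 0 to 5 scale and the margin as printed, and on the decision rule assumed above. It does not depend on the assumed SDs, because the bound in Step 3 uses the largest SD possible. No objection to the JOA margin is made here.

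**What to change.** Amend Table 2 and its text, with a date, before any between-group results are seen:

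- Remove the muscle strength and sphincter function rows and make no non-inferiority claim on either.
- Report muscle strength as the between-group difference in grade with its 95% CI. Report sphincter function as the risk difference in the proportion impaired, with its 95% CI.
- If a muscle strength margin is kept, state how the grades are combined, set the margin well inside the 0 to 5 scale, and justify it.
- State the unit of the VAS margin. If it is 5 mm, give the reason for it and the SD assumed.

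The cost is a table and text edit. No patients, visits or data are added, and the primary analysis does not change. The trial gives up non-inferiority claims on two secondary outcomes that had no evidential value as written.

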### Ethics and dissemination

2.13.

The study will be performed in accordance with the Declaration of Helsinki. This article describes a protocol for a prospective, non-inferiority randomized controlled trial to examine the safety, efficacy, and cost-effectiveness of PMTT vs. LP in treating spinal IDEM tumors. This study was approved by the Ethical Committee of Fujian Medical University Union Hospital, Fuzhou, China, in June 2021(2021YF022-01). Informed consent will be obtained from all eligible participants prior to randomization. The results of the research will be published in international peer-reviewed journals and disseminated through presentations at scientific conferences.

## Discussion

3.

The FJMUUH05 trial is a multicenter RCT, the first RCT of surgery for spinal IDEM tumors. To date, similar RCTs have not been reported on this topic. The trial was approved by the Chinese Clinical Trial Registry (ChiCTR, www.chictr.org.cn). The trial hypothesis is that PMTT has superior cost-effectiveness and is equivalent in safety and efficacy to LP for treating spinal IDEM tumors.

Tubular spinal surgery has gained significant prominence because of the development of minimally invasive technologies and instruments. The tubular retractor is inserted to reach the operation field by separating the paravertebral muscle and exposing the pathological lesions. This technology allows surgeons to remove tumors with two-handed operations and simultaneously use multiple microscopic instruments. Moreover, intraoperative three-dimensional imaging is another massive shift from endoscopic technology, which lets the operator conveniently operate the imaging apparatus, thereby reducing the complication rates of dural rupture. Compared with traditional surgery, fewer clinical studies have been conducted on the selection of surgical indications. The safety and effectiveness of the operation and the treatment of complications during and after the operation lack a unified opinion. The patients will be randomized to the PMTT or LP groups after tumor resection. The trial aims to study the clinical results of PMTT vs. LP for spinal IDEM tumors. This RCT study provides high-quality evidence for the efficacy of tubular spine surgery for spinal IDEM tumors. We believe that the FJMUUH05 trial will provide useful information on the long-term effects of the two treatments for spinal IDEM tumors. To date (October 2021), 11 patients have been included in the trial.

In conclusion, the FJMUUH05 trial is a multicenter RCT investigating the cost-effectiveness, safety, and effectiveness of PMTT and LP in spinal IDEM tumors. When this trial is completed with the hypothesis confirmed, it will popularize the application of PMTT and improve patient outcomes.

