## Introduction

1.

Although spinal intradural extramedullary (IDEM) tumors grow slowly, the spinal canal is limited by its small volume, and the spinal cord and nerve roots are compressed or invaded by the tumor, which causes sensory, motor, and autonomic dysfunction (1). The treatment of spinal IDEM tumors focuses on removing tumor tissue and decompressing the nerve root and spinal cord to improve nerve function (2, 3). Traditional surgical methods include laminectomy (total laminectomy and hemilaminectomy), laminotomy, and laminoplasty (LP) (4). Among the available spinal surgeries with different indications, a “standard surgical procedure” for treating spinal IDEM tumors has not been determined. Owing to the development of minimally invasive spine surgery (MISS), the paraspinal mini-tubular technique (PMTT) has been introduced for treating IDEM tumors (5–7). Most studies reported that tubular spine surgeries reduced the volume of estimated blood loss (EBL) and shortened the length of hospital stay. The postoperative outcome of the patients was good, with fewer complications. These together promoted the development of MISS. A microscope-assisted PMTT has a larger operating space than endoscopy and a relatively wide range of indications, including various types of intervertebral disc herniation, spinal stenosis, spinal tumors, and spinal cord injuries (8). With the popularization and application of PMTT, the safety and effectiveness of treating spinal-related diseases have been increasingly recognized. Compared with traditional surgery, the microscope-assisted microtubular technique has the advantages of less tissue damage, fewer complications, shorter length of hospital stay, reduced postoperative pain, improved surgical efficiency, and reduced risk of spinal instability (9–11). To the best of our knowledge, prospective, randomized controlled trial studies with a large sample comparing the safety and effectiveness of the PMTT and LP in the treatment of spinal IDEM tumors, have not been conducted. Therefore, this study aims to explore the difference in the therapeutic effect of the PMTT and LP in the treatment of patients with spinal IDEM tumors through a prospective, multi-centered, non-inferiority randomized clinical trial. The main hypothesis is that PMTT has advantages in cost-effectiveness, and it is equivalent in safety and efficacy to LP.

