### Study description

2.1.

The FJMUUH05 trial is designed as a prospective, multi-center, non-inferiority RCT with two parallel groups in eight hospitals from seven provinces in China. A total of 280 patients aged 10–75 years with confirmed radiographic diagnosis and IDEM tumor lengths of less than three segments will be enrolled in this study. After the patients sign a written informed consent to participate, they will be randomized to one of the two groups: the PMTT group, which will receive paravertebral approach and microtubular technique treatment, and the LP group, which will receive laminoplasty treatment. The follow-up period will last for two years. The study is registered at https://www.chictr.org.cn, which can be accessed online (ChiCTR2100047582). Consent (version date January 21, 2021, V.1.0) will be obtained by an investigator who will comply with applicable regulatory requirements and adhere to the ethical principles of the Declaration of Helsinki. The time points, randomization, treatment allocation, and assessment are summarized in Figure 1.

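### The main hypothesis claims equivalent safety, but complications and adverse events have no margin and no criterion by which equivalence could be judged

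*Protocol article*

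**What the plan says.** - **Hypothesis.** The Introduction states: "The main hypothesis is that PMTT has advantages in cost-effectiveness, and it is equivalent in safety and efficacy to LP". The Discussion repeats that PMTT has the better cost-effectiveness and "is equivalent in safety and efficacy to LP".
- **Design.** Section 2.1 describes a "prospective, multi-center, non-inferiority RCT with two parallel groups".
- **Margins.** Section 2.12 states: "Non-inferiority margins will be set as listed in Table 2". Table 2 has four rows: JOA, VAS, muscle strength test and sphincter function test, each with a margin of 5.
- **Outcomes outside Table 2.** Section 2.10 begins "Secondary outcomes include the gross tumor resection(GTR) rate, tumor recurrence rate" and goes on to include complications. Section 2.10.1 lists adverse events. None of these has a margin.
- **Analysis.** In section 2.12, "Categorical variables will be compared using" leads to chi-square or Fisher's exact tests, and "Statistical significance will be set at" leads to p<0.05. The same section plans point estimates (odds ratios for categorical outcomes), 95% CIs and p-values for every comparison.

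**The concern.** The article fixes three things that do not fit together: a hypothesis of equivalent safety, a closed list of margins that leaves out complications and adverse events, and tests of difference for categorical outcomes. A test of difference can reject equality but cannot establish equivalence. An interval can support equivalence only when it is compared with a limit, and no limit is given for these outcomes.

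The Discussion expects that confirming the hypothesis will spread the use of PMTT. If confirmation of the safety part came down to a p-value above 0.05, an important excess of CSF leak, infection or other complications could be reported as equivalent safety. The same gap affects the efficacy half of the hypothesis, because resection and recurrence also lack a margin.

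**Working it through.** **Step 1: match the hypothesis to the decision rules.**

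| Outcome | Margin in Table 2 | Test named in 2.12 | Criterion for equivalence |
|---|---|---|---|
| JOA, VAS, muscle strength, sphincter function | 5 | by variable type | non-inferiority margin (one-sided) |
| Complications, adverse events | none | chi-square or Fisher | none |
| Gross tumor resection, recurrence | none | chi-square or Fisher | none |

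Even the first row supports non-inferiority rather than two-sided equivalence.

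**Step 2: the plan's own figure.** The only size calculation (section 2.11) is for JOA: 112 per group, 280 in total. With margin 5, SD 5.8, no true difference, 90% power and one-sided 0.025, n = 2 × (5.8 × (1.960 + 1.282) / 5)² = 28.3, so 29 per group. At one-sided 0.05 it is 24. The stated 112 is not reproduced, but that is a separate matter. Here 112 and 280/2 = 140 serve only as the lower and upper arm sizes. The plan has no figure for safety to reproduce.

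**Step 3: power of the planned difference test.** The article gives no event rates, so those below are assumptions. Power is taken at two-sided 0.05; the article does not state sidedness.

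Power = Φ{ [ |p₂ − p₁|√n − 1.96√(2p̄(1 − p̄)) ] / √(p₁(1 − p₁) + p₂(1 − p₂)) }

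- 10% v 20%, n = 112: (0.10 × 10.583 − 1.96 × 0.5050) / 0.5000 = 0.137, power 55.5%.
- 10% v 20%, n = 140: (0.10 × 11.832 − 1.96 × 0.5050) / 0.5000 = 0.387, power 65.1%.
- 5% v 10%, n = 112: (0.05 × 10.583 − 1.96 × 0.3725) / 0.3708 = −0.542, power 29.4%.
- 5% v 10%, n = 140: (0.05 × 11.832 − 1.96 × 0.3725) / 0.3708 = −0.373, power 35.4%.

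A true rise from 10% to 20% is therefore non-significant in about 35% to 45% of trials, and one from 5% to 10% in about 65% to 71%. Exact Fisher power is lower: 49% to 59% and 22% to 27% respectively.

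**Step 4: width of the interval when the arms are truly equal.** The half-width for the risk difference is 1.96√(2p(1 − p)/n). At p = 10%:
- n = 112: 1.96 × √(0.18/112) = 7.9 points.
- n = 140: 1.96 × √(0.18/140) = 7.0 points.

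An observed 10% in both arms would still be compatible with an excess of 7 to 8 points. Over equal rates of 5% to 20%, the half-width runs from about 5 to 10.5 points.

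**Step 5: could a safety margin be met at this size?** With equal true rates of 10%, one-sided 0.025 and 80% power, n = (1.960 + 0.842)² × 2 × 0.1 × 0.9 / margin². The two margins are illustrations, not proposals.
- 10 points: 7.849 × 0.18 / 0.0100 = 141.3, so 142 per arm.
- 5 points: 7.849 × 0.18 / 0.0025 = 565.1, so 566 per arm.

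At a 5% rate the corresponding figures are 75 and 299 per arm. A wide margin is within reach only at low event rates. A 5-point margin is out of reach at every rate tried (5% to 20%).

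**The case against.** The case on the other side is substantial, and much of it stands.

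- **No rule equates non-significance with equivalence.** A reader might infer that the authors intend to treat p≥0.05 as proof of equal safety. The article does not say so. It sets a significance threshold and is silent on what p≥0.05 means. The supportable statement is that such a reading is left open.
- **The p-value is not the only output.** Section 2.12 already plans odds ratios with 95% CIs, and an honest interval would show readers what is not excluded. That is correct. But without a margin the interval supplies no criterion for the hypothesis, and an odds ratio alone does not show the absolute excess.
- **Safety is not wholly uncovered.** Muscle strength and sphincter function have margins, and the JOA includes clinical signs and bladder function, so neurological harm is partly addressed. Whether 5 is a useful margin on a muscle scale of zero to five is a separate question. These measures do not cover CSF leak, infection, hematoma or thromboembolism.
- **Resection and recurrence are listed apart from complications.** They belong with the efficacy half of the claim, not the safety half.
- **Secondary decision rules often sit in an SAP, and secondary outcomes are often not powered.** Both are true, and low power for complications is not itself a fault here. The point is narrower: the published hypothesis, margin list and tests do not match, and the hypothesis wording is in this article.

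**Conclusion.** The concern holds in a limited form. The plan as written has no analysis that could confirm equivalent safety for complications and adverse events, or equivalence for resection and recurrence, although the main hypothesis claims equivalent safety and efficacy. The arm sizes make the gap matter: for assumed rates of 10% v 20%, about 35% to 45% of trials would be non-significant, and at 10% in both arms the interval is about ±7 to 8 points. These sizes rest on assumed rates, on chi-square power at two-sided 0.05, and on 112 to 140 patients per arm. The mismatch itself rests on none of them.

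The documents do not support a stronger conclusion that the authors have adopted non-significance as their test of equivalence, or that no harm outcome has any margin. The primary JOA comparison is unaffected. The change should be made, because it governs what the trial can claim about safety.

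**What to change.** 1. **Introduction and Discussion:** reword the hypothesis to non-inferiority on JOA, with complications, resection and recurrence estimated rather than claimed equivalent. Alternatively, prespecify a justified margin for a named safety outcome and judge it by the confidence interval. Step 5 shows that the present size may not support one.
2. **Section 2.12:** state that p≥0.05 will not be read as equivalence or non-inferiority, and that outcomes without a margin will be interpreted from their 95% CIs.
3. **Section 2.12:** add the absolute risk difference (PMTT minus LP) with its 95% CI to the planned odds ratio for complications, resection and recurrence.

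The rewording route costs some text and routine output, with no added patients or visits. Its downside is a more modest safety claim.
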